### Sample size {14}

The objective of this trial is to evaluate whether evolocumab effectively prevents post-CABG myocardial injury in patients with multivessel CAD. The peak Troponin-I level during the first three postoperative days compared to the initial level was evaluated as the primary outcome. Based on studies by Kaushik et al. on the efficacy of statin in preventing myocardial injury in CABG patients, the difference between peak Troponin-I versus initial level was 1.00±1.34 ng/mL in the statin loaded group and 2.25±2.59 ng/mL in the control group [6]. Therefore, with the power of 0.8 and significance level of 0.05, the change of Troponin-I at the time of peak compared to the base point can be calculated as 1.00±1.34ng/mL in the evolocumab group and 2.25±2.59ng/mL in the control group. According to the Power Analysis & Sample Size (PASS) 16 program, a minimum of 45 people per group are required for validation and a potential dropout rate of 10%, 50 people per group, and a total of 100 people are required for this clinical trial.

### Recruitment {15}

Patients will be recruited from outpatient clinics and referrals from other departments during admission from the Catholic University of Korea’s Seoul St. Mary’s Hospital and Eunpyeong St. Mary’s Hospital.

## Assignment of interventions: allocation

### Sequence generation {16a}

Subjects who agree to participate in this trial will sequentially receive subject identification codes in the order of their screening visit. Patients are randomly assigned to ensure scientific validity, maximize comparability between groups, and avoid bias. Those who meet the eligibility criteria will be divided into two groups, with the stratified block randomization method used due to multi-institutional sampling. An independent statistician will produce random allocation numbers using the Statistical Analysis System (SAS) ver. 9.4, Microsoft Windows (SAS Institute Inc., Cary, NC, USA), which will then be distributed to the subjects.

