### Trial design {8}

In this randomized, phase III superiority controlled clinical trial, patients will be randomly assigned in a 1:1 ratio to one of two groups: a test group (evolocumab (140 mg) administration once within 72 h before CABG) and a control group (no administration). Daily blood tests will be performed during hospitalization, including those assessing cardiac markers, while major postoperative complications will be evaluated for 1 month. Medications such as aspirin and P2Y12 inhibitors (clopidogrel, prasugrel, ticagrelor) and recommended dose (2018 ACC/AHA guidelines) of statins will be given unless contraindicated [23].

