## Statistical methods

### Statistical methods for primary and secondary outcomes {20a}

Statistical methods for this clinical trial will be two-tailed tests with a significance level of 0.05. Continuous variables will be presented as descriptive statistics (average, standard deviation, median, minimum, and maximum). Categorical variables will be presented as descriptive statistics (frequency and percentage).

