#### Primary efficacy evaluation

The maximum change in troponin-I between peak and baseline during the first 3 days will be presented as descriptive statistics and tested with an independent t-test or Wilcoxon’s rank-sum test.

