#### Secondary efficacy evaluation

AUC (area under the ROC curve) of both troponin-I and CK-MB for 3 days and maximum change of CK-MB over 3 days compared to baseline level after evolocumab administration will be tested with independent t-test and Wilcoxon’s rank sum test. Changes in troponin-I levels at each visit compared to the initial level will be analyzed with repeated ANOVA.

Changes in CK-MB, brain natriuretic peptide (BNP), and CRP level compared to baseline levels will be analyzed with repeated ANOVA.

Changes in left ventricular ejection fraction at 3 days from baseline will be analyzed with an independent t-test and Wilcoxon’s rank-sum test. For comparison within the group, a paired t-test or Wilcoxon’s signed rank test will be used.

Cumulative mortality, recurrence rate of myocardial infarction, incidence of stroke, new atrial fibrillation, and incidence of coronary revascularization 1 month after the procedure will be analyzed using the Kaplan-Meier method. Differences between the two groups will be tested using the log-rank test. In this analysis, no missing values will be used.

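### Allocation is stratified because of the two hospitals, but the named tests carry no hospital term and do not use baseline as a covariate; this may cost power and does not threaten validity

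*Protocol article*

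**What the plan says.** All references are to the protocol article.

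- **Design.** Trial design {8}: "patients will be randomly assigned in a 1:1 ratio to one of two groups". Sequence generation {16a}: eligible patients are divided into the two groups, "with the stratified block randomization method used due to multi-institutional sampling". Study setting {9} names two hospitals of one university. The stratification factor is not named in so many words, but the reason given points to hospital and to nothing else.
- **Primary test.** Primary efficacy evaluation: the largest change in troponin-I over three days is "tested with an independent t-test or Wilcoxon" rank-sum test. Statistical methods {20a} sets "two-tailed tests with a significance level of 0.05".
- **Secondary tests.** Secondary efficacy evaluation applies the t-test and the rank-sum test to the AUCs and to maximum CK-MB change, and repeated ANOVA to the visit-wise changes in troponin-I, CK-MB, BNP and CRP. For LVEF: "Changes in left ventricular ejection fraction at 3 days from baseline will be analyzed with an independent t-test" and the rank-sum test. For clinical events: "Differences between the two groups will be tested using the log-rank test".
- **Other analyses.** Section {20b} adds none. The sensitivity analyses in {20c} concern non-adherence, not adjustment.

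None of these places mentions a hospital term, a stratified test or a baseline covariate.

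**The concern.** Blocking within hospital makes the arms alike in their hospital mix. The treatment difference then does not vary because of hospital, but a two-sample test still counts between-hospital spread as random error. If that spread is real, the reported standard error is larger than the true one, the interval is too wide, and the test rejects a true null less often than 5%. Part of the precision that the stratification provides is not used.

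Baseline raises a second, separate matter. Subtracting the baseline value fixes its coefficient at 1, whereas using it as a covariate lets the data set the coefficient. Apart from the degree of freedom spent, the covariate analysis is at least as precise, and it also corrects for chance baseline imbalance.

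The stake is efficiency in a trial planned at 80% power with 45 evaluable patients per group.

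**Working it through.** **1. The plan's own figure.** Sample size {14} assumes "1.00±1.34ng/mL in the evolocumab group and 2.25±2.59ng/mL in the control group", "with the power of 0.8 and significance level of 0.05".

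- Difference: 2.25 − 1.00 = 1.25 ng/mL.
- Root-mean-square SD: √((1.34² + 2.59²)/2) = √4.252 = 2.062.
- Normal approximation: n = 2(1.960 + 0.842)² × 4.252 / 1.25² = 42.7, so 43 per group.
- Noncentral t: 44 with pooled variance, 45 with Welch (power 0.7998 at 44 and 0.809 at 45).
- Dropout: 45 / 0.9 = 50 per group, 100 in total.

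The stated 45 and 100 reproduce. The sample size is not in error.

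**2. Leaving hospital out of the primary test.** Let R² be the share of within-arm outcome variance that hospital explains. The documents do not give it, so a range is assumed. With arms balanced within hospital, the true SE is √(1 − R²) times the SE the unadjusted test uses. That test's SE is therefore too wide by the factor 1/√(1 − R²), and its approximate type I error is 2[1 − Φ(1.96/√(1 − R²))].

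Example at R² = 0.10: 1/√0.90 = 1.054, and 2[1 − Φ(2.066)] = 0.039.

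Simulation: 20,000 trials per cell, 46 per group (chosen so that two equal hospitals split evenly within arm), normal outcome, total SD 2.062 in both arms, effect 1.25.

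| R² (assumed) | SE too wide by | Type I, unadjusted | Power, unadjusted | Power, hospital-adjusted | Points lost |
|---|---|---|---|---|---|
| 0 | 0% | 5.1% | 82.0% | 81.9% | 0 |
| 0.05 | 2.6% | 4.5% | 82.6% | 83.9% | about 1 |
| 0.10 | 5.4% | 4.0% | 83.5% | 86.2% | about 3 |
| 0.20 | 11.8% | 2.9% | 84.1% | 89.0% | about 5 |

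The adjusted model stays at about 5.1% type I error throughout.

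**3. The same check on the log scale.** Every input here is an assumption except the log SD, which converts the control-arm figures: √ln(1 + (2.59/2.25)²) = 0.92. The assumptions are 46 per arm, hospitals split 28/18 within each arm, a 45% reduction, and 0.92 as the within-hospital SD.

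- Hospitals alike: power 87% unadjusted, 87% adjusted.
- One hospital at twice the other: type I 3.6% against 4.9%; power 84% against 87%.
- Three times: type I 2.3% against 4.8%; power 79% against 87%.

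The pattern is the same. The threefold case corresponds to R² = (ln 3)² × 0.609 × 0.391 / [that + 0.92²] = 0.287/1.134 ≈ 0.25, just beyond the range in step 2.

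**4. Baseline as covariate.** With SDs s_b at baseline and s_f at follow-up, and correlation r, the ratio of ANCOVA variance to change-score variance is s_f²(1 − r²) / (s_f² + s_b² − 2r·s_f·s_b).

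- *LVEF.* It is measured at V1 and V6 (Table 1) and entry does not restrict it. If the two SDs are equal (assumed), the ratio becomes (1 − r²)/(2(1 − r)) = (1 + r)/2: 0.65, 0.75 and 0.85 at r = 0.3, 0.5 and 0.7.
- *Troponin-I and CK-MB.* Eligibility criteria {10} require both to be within normal range at entry, and the Discussion expects enzymes to rise in almost all patients, so equal SDs are not credible. For troponin-I with s_b between 0.005 and 0.05 (assumed) and s_f = 2.062, the SE ratio is 1.00 at r = 0, about 0.95 to 0.96 at r = 0.3 and 0.87 to 0.88 at r = 0.5. The documents do not give r, so the gain may be nil.
- *Sensitivity to the SD ratio.* With s_f = 5s_b, the variance ratio is 25(1 − r²)/(26 − 10r): 0.99 at r = 0.3 and 0.67 at r = 0.7. The LVEF figures therefore do not carry over to the enzymes.

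**The case against.** **Model terms belong in the analysis plan, which is not shown.** This has force for repeated ANOVA, where the article lists no factors, so its silence is not a decision. It has less force for the primary outcome: the article names two-sample tests, and in their ordinary form they do not follow the stratified allocation.

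**The loss is conditional.** This stands. Both hospitals belong to one university, and nothing in the documents shows that their assays, technique or patients differ. The loss may be close to zero.

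**Baseline is not ignored.** This also stands. The primary outcome, maximum CK-MB change, all visit-wise outcomes and LVEF change already subtract it. A reader might infer that every stated test disregards baseline, but among the continuous outcomes that fits only the AUCs. The accurate point is that baseline is subtracted rather than used as a covariate.

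**Inference stays valid.** Agreed. A reader might infer from the mismatch that the result would be biased, that type I error would be inflated or that the trial is undersized. None of these follows: the error is conservative, and the sample size reproduces.

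**No benefit is shown for a stratified log-rank test.** Agreed. No calculation supports one for 30-day events in 100 patients.

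**Conclusion.** The point holds as an efficiency matter. The design stratifies because of the hospitals, and the named analyses do not use that stratum or a baseline covariate. On the protocol's own difference and SDs, omitting hospital costs the primary test about 0, 1, 3 or 5 points of power when hospital explains 0, 5, 10 or 20% of the variance. Those shares are assumed, because the documents do not give the hospital effect. That hospital is the stratum is inferred from the stated reason for stratifying.

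The gain from a baseline covariate is clearest for LVEF, subject to the equal-SD assumption, and uncertain for troponin-I and CK-MB. The change is worth making because adjustment costs nothing measurable when hospitals do not differ (82.0% against 81.9%).

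**What to change.** - **Primary outcome.** Fit a linear model with treatment, hospital and baseline troponin-I, on the log scale if the data are skewed. The log scale turns the treatment effect from a difference in ng/mL into a ratio, so the choice of scale should be fixed in advance. Use a hospital-stratified (van Elteren) rank test as the non-parametric version.
- **Continuous secondary outcomes.** Include hospital and the corresponding baseline value as terms in the models for LVEF, CK-MB, BNP, CRP, visit-wise troponin-I and the AUCs.
- **Clinical events.** Stratifying the log-rank test by hospital is optional.
- **Wording.** Name hospital as the stratification factor in Sequence generation {16a}, if that is what it is.

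The cost is wording in the analysis sections and one or two degrees of freedom out of 88 (2 × 45 − 2). No new data and no change to the sample size are needed. The trial is open-label, so the change should be made before outcome data are examined by arm.

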### Concealment mechanism {16b}

Allocation is concealed in a sealed envelope.

### Implementation {16c}

In this trial, the test group will receive a subcutaneous injection of 140 mg of evolocumab, 72 h prior to surgery. The control group will not receive any placebo or medication.

## Assignment of interventions: blinding

### Who will be blinded {17a}

Patients and investigator will not be blinded.

### Procedure for unblinding if needed {17b}

The trial is open and there is no unblinding procedure.

## Data collection and management

### Plans for assessment and collection of outcomes {18a}

Efficacy and safety evaluation outcomes of this clinical trial are assessed according to the following variables:

#### Primary efficacy evaluation variable

Maximum change in troponin-I between baseline and peak level during the first 3 days after coronary artery bypass grafting

#### Secondary efficacy evaluation variables

AUC (area under the ROC curve) of troponin-I for 3 days after administration of evolocumabTroponin-I level change at each visit compared to baseline levelMaximum change of CK-MB during the first 3 days after coronary artery bypass grafting compared to baseline levelAUC of CK-MB (creatine kinase MB) for 3 days after administration of evolocumabChange in CK-MB levels at each visit compared to baseline levelChange in BNP (brain natriuretic peptide) levels at each visit compared to baseline levelChange in CRP (C-reactive protein) level at each visit compared to baseline levelChange in LVEF (left ventricular ejection fraction) 3 days after the procedure compared to baseline levelCumulative mortality during a 1-month period after surgeryCumulative recurrence rate of myocardial infarction during the first month after the procedureCumulative incidence of stroke (hemorrhagic stroke, ischemic stroke, transient ischemic attacks) during the first month after the procedureCumulative incidence of new atrial fibrillation during the first month after the procedureCumulative incidence of coronary revascularization (PCI or CABG) during the first month after the procedure

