## Abbreviations

ADL: Activities of daily living
AE: Adverse event
ALT: Alanine transaminase
AST: Aspartate transaminase
AUC: Area under the curve
BNP: Brain natriuretic peptide
BUN: Blood urea nitrogen
CABG: Coronary artery bypass grafting
CCRC: Clinical Case Review Committee
CK-MB: Creatine kinase MB isoenzyme
DCC: Data coordinating center
DCFs: Data Clarification Form
EC: Executive Committee
ECG: Electrocardiogram
eCRF: Electronic case report form
F/U: Follow-up
FAS: Full analysis set
GCP: Good Clinical Practice
HCG: Human chorionic gonadotropin
HDL: High-density lipoprotein cholesterol
hsCRP: High-sensitivity C-reactive protein
ICH: International Conference on Harmonization
IRB: Institutional Review Board
ITT: Intention to treat
IWRS: Intracive web-based response system
LDL: Low-density lipoprotein cholesterol
LVEF: Left ventricular ejection fraction
MFDS: Ministry of Food and Drug Safety
Op: Operation
PCI: Percutaneous coronary intervention
PCSK9: Proprotein convertase subtilisin-kexin type 9
PPS: Per protocol set
SAE: Serious adverse event
SOP: Standard operating procedure

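### The troponin-I and CK-MB AUC endpoints are defined as ROC areas over a window that starts at an injection controls never receive and can end as early as the start of surgery

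*Protocol article*

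**What the plan says.** All references are to the protocol article.

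- **Secondary efficacy evaluation variables:** the first item is "AUC (area under the ROC curve) of troponin-I for 3 days after administration of" evolocumab. The CK-MB AUC item uses the same three days counted from the injection, without the ROC gloss. In the same list, the maximum change in CK-MB is counted from bypass grafting.
- **Secondary efficacy evaluation (statistical methods):** "AUC (area under the ROC curve) of both troponin-I and CK-MB for 3 days and maximum change of CK-MB over 3 days" are to be compared by independent t-test and Wilcoxon rank-sum test. Here the injection is the stated starting point for the CK-MB maximum change as well.
- **Abbreviations:** "AUC: Area under the curve", with no mention of ROC.
- **Trial design {8}:** the arms are "a test group (evolocumab (140 mg) administration once within 72 h before CABG) and a control group (no administration". Implementation {16c} adds that controls get neither placebo nor drug.
- **Injection time:** Trial design {8}, the Abstract and the choice-of-comparators section {6b} allow any time within the 72 hours before CABG. Implementation {16c} gives it as "72 h prior to surgery", and Limitations uses similar wording.
- **Primary efficacy evaluation variable, Table 1 and Discussion:** all three count the three days of marker measurement from CABG. Table 1 places V2 to V6 at 0, 6, 24, 48 and 72 h after the operation in both arms.

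**The concern.** Two parts of the definition are wrong as written: the quantity and the window.

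An ROC area summarises how well a marker separates two groups of patients. It is one number for a set of patients, so there are no individual values for a t-test or rank-sum test to compare.

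The window starts at an event that happens in only one arm. In the treated arm, any gap between injection and surgery replaces postoperative hours with preoperative ones, although the endpoint is meant to capture marker release caused by the operation. In the control arm the analyst has to supply a start time that the plan does not give. The trial is open-label, so that start time should be fixed in writing before the data are seen.

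**Working it through.** The plan states no numerical figure for the AUC endpoints, so there is none to reproduce. Its sample size concerns the primary outcome and does not enter here.

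**Step 1: the quantity.** The outcome list says ROC for troponin-I, and the statistical methods say ROC for both markers. The abbreviation list says only area under the curve. The planned tests need one value per patient, which the area under a concentration-time curve supplies and an ROC area does not. The stated definition and the stated test are therefore incompatible.

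**Step 2: the time origin.**

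| Item | Counted from |
|---|---|
| Primary outcome, maximum troponin-I change | CABG |
| CK-MB maximum change, outcome list | CABG |
| CK-MB maximum change, statistical methods | Injection |
| Troponin-I and CK-MB AUC, outcome list | Injection |
| Table 1, V2 to V6 | Operation |
| Rationale in the Discussion | CABG |

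The injection-based origin conflicts with the rest of the document and, for CK-MB maximum change, with the plan's own outcome list. Controls have no injection, so their AUC window has no start.

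**Step 3: postoperative coverage in a treated patient.** Inputs:

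- window length of 72 h (three days);
- lead time L from injection to surgery, between 0 and 72 h (Trial design {8}; Table 1 enrolment window);
- nominal sampling times of 0, 6, 24, 48 and 72 h (Table 1).

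Surgery is treated as a single reference time, because the documents give no operating time.

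Postoperative hours in the window = 72 − L. Share of the 0 to 72 h period = (72 − L)/72.

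| L (h) | Window ends, h after surgery | Share | Nominal samples inside |
|---|---|---|---|
| 0 | 72 | 100% | 0, 6, 24, 48, 72 |
| 12 | 60 | 83% | 0, 6, 24, 48 |
| 24 | 48 | 67% | 0, 6, 24, 48 |
| 36 | 36 | 50% | 0, 6, 24 |
| 48 | 24 | 33% | 0, 6, 24 |
| 60 | 12 | 17% | 0, 6 |
| 72 | 0 | 0% | 0 only |

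Any lead above 0 h drops the nominal 72 h sample, and any lead above 24 h also drops the 48 h sample. Table 1 schedules no marker sample between V1 and V2, so the preoperative part of the window contains only the baseline value. Taken literally, the wording in Implementation {16c} would put every treated patient in the last row.

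**Step 4: the control arm.** The plan gives no rule, so any choice is an assumption.

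- *Counted from surgery:* controls contribute the full 72 postoperative hours and treated patients 72 − L, which would artificially favour evolocumab.
- *Counted from allocation:* both arms lose postoperative release, by an amount set by operating-room scheduling.

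Neither choice makes the injection-anchored AUC a clean measure of postoperative release.

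**The case against.** The strongest reply is that both phrases are slips and the intent is plain. The abbreviation list has no ROC, the CK-MB item in the outcome list omits it, and the tests make sense only for a per-patient exposure. Every postoperative sample is timed from the operation. The statistical methods attach the injection to the CK-MB maximum change, which the outcome list counts from CABG, so the phrase looks loosely used. An analyst would probably compute the right thing. This stands as evidence of intent and lowers the severity. It does not remove the error: the wrong quantity appears in two sections, the wrong origin is attached to both markers, and an endpoint definition should not depend on the analyst overriding it.

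A reader might go further than the documents allow in three ways.

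- **That the window can end before surgery.** With injection at most 72 h before CABG, a 72 h window ends at surgery at the earliest. It would end sooner only if the operation were delayed beyond the stated limit.
- **That the analysis is biased towards evolocumab.** This holds only if controls are counted from surgery, which no section says. Read literally, the control AUC is undefined and the direction of any bias is unknown.
- **That all postoperative release is lost in the treated arm.** This is the extreme at L = 72. The documents give no distribution of lead times.

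The interpolation rule and the analysis scale for the AUC are ordinary matters for an analysis plan and are not part of this point.

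**Conclusion.** The point holds as a should-fix. The two AUC endpoints name a quantity that the planned tests cannot use, and their window has no start in one arm and variable postoperative coverage in the other. That coverage is 72 − L hours, from the full 72 h down to none. It rests on the stated 0 to 72 h dosing limit, nominal sampling times and a single reference time for surgery.

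The AUCs are two of thirteen listed secondary variables. The CK-MB maximum change is a third whose wording is inconsistent between the outcome list and the statistical methods. The primary outcome, its test, the sample size and the data collection are not touched.

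**What to change.** In both Secondary efficacy evaluation variables and Secondary efficacy evaluation:

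1. Replace the ROC wording. Define the troponin-I and CK-MB AUCs as the area under the concentration-time curve from 0 to 72 h after CABG, using V2 to V6.
2. State one surgery-based time origin that applies to both arms.
3. In the statistical methods, count the CK-MB maximum change from CABG, as the outcome list already does.

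Separately, the injection time is worded differently in the Abstract, Trial design {8}, the choice-of-comparators section {6b}, Implementation {16c} and Limitations. These sections must be reconciled; this review takes no position on which wording is right.

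The cost is wording only. V2 to V6 already supply the samples in both arms, so no visit, test or patient is added.
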